## Abstract

(1) Background and objective: Cardiac rehabilitation (CR) means delivering health education by structured exercises with the means of risk reduction, in a cost-effective manner. Well-conducted CR improves functional capacity, decreases re-hospitalization, and reduces mortality up to 25%. We bring to attention the protocol of a randomised control trial with the aim of validating the prototype of an assistive upper-body robotic exoskeleton system enhanced with a non-immersive virtual reality exergame (CardioVR-ReTone) in patients who undergone cardiac surgery. (2) Methods: Description of the CardioVR-ReTone system and the technical specification, followed by the group selection, randomization and evaluated variables. (3) Expected results: The primary outcome measurement is the modification of life quality at the end of the CR exercise training program. Secondary outcomes will encompass measurements of sternal stability, muscular activity, cardiac response to exercise, pain level and compliance/adherence to CR. (4) Conclusions: Implementing these novel features of the CardioVR-ReTone system, addressability, and efficacy of CR, so problematic in certain situations and especially in cardiac surgery, will be greatly facilitated, being independent of the skills and availability of the rehabilitation therapist.

## 1. Introduction

The burden of cardiovascular diseases (CVDs) is high, in 2015 being estimated 422.7 million cases that led to 17.92 million deaths [1]. Thus, CVDs are the main cause of mortality in the middle-aged population worldwide [2].

Cardiac rehabilitation (CR) means delivering health education by structured exercises by means of risk reduction, in a cost-effective manner. Well-conducted CR improves functional capacity, decreases re-hospitalization, as well as reducing mortality up to 25% [3]. A suitable rehabilitation is essential for enabling those people to live independently and enhance their quality of life (QoL) as they age. Most of these rehabilitation treatments need sessions of rehabilitation therapy to fortify muscles, to improve the motion of joints, to restore cardiac functional capabilities, and to globally increase freedom of movement [4,5]. In order to be time efficient, a CR therapy after open cardiac surgery should start in hospital and continue partly under supervision, partly at home, for 2 to 6 weeks [5,6]. The continuity of care is often interrupted in the transition from hospital to home due to the limited number of qualified human therapists that should supervise the CR. The demand for qualified kinesitherapies is growing, particularly as the Western population is aging. In the absence of a trained therapist, the patients loses his motivation for exercising, and they tend to become tired or bored by a monotonous training process [7]. Moreover, according to Kraal J.J. et al. the cost of rehabilitation therapies rises worldwide each year. For example, in Denmark, in 2018, motor rehabilitation therapy throughout 3 weeks following heart valve surgery exceeded 20,000 € per patient [8].

Because of these high costs, most of the patients lack the opportunity of rehabilitation therapy. While there remain a few procedures that only human therapists can undertake, many rehabilitation exercises are highly repetitive [9]. This is where robotic systems outperform the humans. They can perform the same task (s) with high precision and without exhaustion or loss of attention and concentration [10]. Nonetheless, the addressability of such robotic exoskeleton systems in delivering therapy after a cardiac open surgery or a major cardiac event is very limited [11,12,13]. The use of digital therapeutic games and virtual reality (VR) platforms as well as coupled with Artificial Intelligent agents in rehabilitation practices are increasing [14].

Despite its repeatedly proven benefits, and the clinical practice guideline recommendations, CR programs are grossly under-used. Worldwide, there is low availability of CR; only 38.8% of countries globally have CR programs [1]. We lack the strategies to increase CR availability at all levels. To surmount these difficulties systematic referral strategies, supportive public health policies and alternative models of delivery should be implemented at national and international levels.

The scope of the trial is to support motor recovery of patients following a cardiac surgery or a major cardiac event to ensure a normal active and independent life. This shall be realised by initiating CR immediately after surgery using an assistive upper-body robotic exoskeleton System enhanced with a non-immersive virtual reality exergame (CardioVR-ReTone). The aim of the clinical trial is to validate the prototype of the CardioVR-ReTone system in patients who have undergone cardiac surgery.

## 2. Materials and Methods

### 2.1. Description of the CardioVR-ReTone Exoskeleton

The basic configuration of the CardioVR-ReTone robotic exoskeleton is highlighted in Figure 1a,b. The CardioVR-ReTone robotic exoskeleton consist of two arms, each has seven degrees of freedom (DOFs). The actuation system for each robotic exoskeleton arm consists of six DC brushed motors such as Maxon EC60fl (Maxon, Sachseln, Switzerland) that assure the necessary torque to each joint through a reducer CPU-17-M (Maxon, Sachseln, Switzerland) CPU-20-M (Maxon, Sachseln, Switzerland), CPU-25-M (Maxon, Sachseln, Switzerland)and in addition each arm contains a passive joint for facilitating the hand rotation. The CardioVR-ReTone robotic exoskeleton is attached to a floor-mounted frame, which allows you to adjust both the height and the distance between the arms as needed.

The exoskeleton has seven rotational joints making possible the following movements: flexion-extension of the shoulder, abduction-adduction of the shoulder, internal-external rotation of the shoulder, elbow flex-extension, pronation forearm-supination, flexion of the wrist extension and radial-ulnar deviation of the wrist. Redundant kinematic mechanisms facilitate flexibility in positioning and orientation due to their possession of more DOF than necessary. Thus, to increase the manoeuvrability of the CardioVR-ReTone, five DOFs are assigned to the shoulder complex, the elbow joint and the radio articular joint are each modelled by a single DOF.

The exoskeletal actuated joints are labelled from 1 to 6 in the order shown in Figure 2, and the passive joint that will allow the wrist radial-ulnar deviation it is not highlighted in the figure.

### 2.2. Space Requirements–Specification

The patient’s cardiac rehabilitation movements should not be restricted by the size and movement capabilities of the CardioVR-ReTone exoskeleton. The minimum space required for the safe use of the CardioVR-ReTone is 1.2 × 2 m^2^.

The technical characteristics (hight, width, footprint and weight) of the CardioVR-ReTone robotic exoskeleton are mentioned in Table 1. The technical characteristics are adapted to the length of the arms and to the movement capabilities. CardioVR-ReTone exoskeleton robotic exoskeleton is capable (Figure 3) to augment the necessary CR movements of the upper body.

The CardioVR-ReTone robotic exoskeleton is capable (Figure 3) to augment the necessary cardiac rehabilitation movements of the upper body.

### 2.3. Setting

#### 2.3.1. Enrolment of the Patients

The trial will be carried out at the Cardiac Surgery Department of one tertiary hospital Institute for Cardiovascular Diseases Timisoara which is a university-affiliated teaching hospital. The participants recruited will undergo cardiac surgery via a median sternotomy. Ethics approval for the study will be obtained from the Etic Committee of University of Medicine and Pharmacy (registration number 350/02.21.2019). Every volunteer will sign an informed consent. The expected number of participants is 30 (an average of five participants recruited/month, for 6 months).

#### 2.3.2. Eligibility Criteria

For the hospitalized patients are age >18 years, agreement to participate by signing informed consent, coronary artery bypass graft surgery, cardiac valve surgery, or both via median sternotomy. The exclusion criteria are insufficient Romanian-language comprehension, debilitating pathology of upper limb/shoulder, musculoskeletal system that limit exercise capacity, moderate to severe chronic obstructive pulmonary disease addiction to alcohol or drugs, symptomatic psychiatric illness (dementia, schizophrenia, acute psychosis) or severe neurological illness (stroke, Parkinson diseases).

#### 2.3.3. Recording of Demographic and Clinical Data

Demographic data: name, file number, age, sex, BMI, the length of the upper arm, blood pressure at both arms, cardiac frequency, SaO_2_, ECG, CPET for aerobic capacity recording before surgery (Table 2).

#### 2.3.4. Establishing Testing Protocol

In order to test the CardioVR-ReTone system and adjust it for post operatory rehabilitation programs a set of standardized exercises, in accordance with rehabilitations guidelines [15] is available (see the Supplementary Files).

#### 2.3.5. Testing the Exoskeleton and Recording the Results

All of the participants will be trained how to use the exoskeleton and the EMG electrodes will be placed following the steps provided by the producer (e.g., Delsys Trigno, Delsys Inc., Boston, MA, USA). All the patients will wear a sternal support. The test will take around 30 min. In the meantime, based on the verbal instructions of each participant, the exoskeleton will be adjusted until they feel comfortable with it and no further adjustment will be necessary. Two unblinded climatotherapists with experience in cardiovascular rehabilitation will train the patients. The movements will be recorded using Optitrack V100:R2 cameras. EMG signals will be recorded using a wireless system (e.g., Delsys Trigno, Delsys Inc., Boston, MA, USA) to quantify muscle activity. The movements will be enhanced by using a non-immersive virtual reality exergame which will be projected on a screen in front of the patient. The VR possibilities are detailed in Figure 4, and the patients can choose which game he/she prefers. The total time of the exercise and the number of repetitive cycles will be registered. Cardiac frequency and SaO_2_ will be monitored and recorded throughout the exercises. The patients’ feedback regarding pain or pressure will be constantly recorded. Pain intensity will be measured every 5 min during the test using the numerical pain assessment scale. The McGill Pain Short Form Questionnaire version 2 will be used to measure pain intensity after the test. The main reasons for terminating the physical training include: the patients’ request to stop due to severe symptoms (i.e., chest pain, shortness of breath or fatigue, palpitations), severe exercise-induced hypotension (<100/50 mmHg) or hypertension (>250/110 mmHg), signs of low cardiac output (pallor, cyanosis, cold extremities, dizziness), neurological signs (confusion, ataxia).

The sternal pain will be differentiated from angina pectoris by clinical evaluation (pain characteristics, duration, and its resolution after antalgic treatment). If the pain persisted after the physical training stopped, EKG and troponins should be measured. To prevent the angina, moderate to high-risk patients because of left ventricular dysfunction, coronary disease severity, comorbidities, ageing: will be starting at 40% of the HR. In case of asymptomatic ischemia consider 40–60% of heart rate reserve at the onset of ischemia. For the patients known with coronary artery disease, prophylactic nitroglycerine will be administered at the start of the training session.

#### 2.3.6. Appling the Clinical Protocol and Recording the Results to Validate CardioVR-ReTone System

The participants will be randomly assigned into two groups: one following CR program with CardioVR-ReTone system and another following a usual CR program (Figure 5). The patients will be allocated to early CR using the Cardio-VR-ReTone System or early CR with the usual physical training, via block randomisation on a 1:1 basis. A designated statistician will randomly allocate patients. A member of the research team will implement the randomisation sequence. The cardiac surgeons and the team members responsible for interpreting the results will be blinded to group allocation. The CR staff responsible for the physical training and the patients will not be blinded. CR will be delivered daily from day 2 after surgery until discharge. The CR program will be fully explained to both groups and will be cautiously monitored by experienced physiotherapists. Each participant will receive a printed and a standardised verbal exercise list delivered by the kinesitherapies. The patients’ feedback regarding pain or pressure will be constantly recorded. Both groups will continue exercising at home without the help of the CardioVR-ReTone system and will be clinically evaluated at 4 weeks after discharge. The Medical Outcomes Study 36-item Short Form Health Survey (SF-36v2) for evaluating the QoL and Modified Sternal Instability Scale (SIS) will be used to assess sternal instability after 4 weeks of training. Results will be recorded as described in an electronic database.

#### 2.3.7. Statistical Analysis

The primary hypothesis will be examined by analysis of variance by repeated measurements to assess postoperative changes from baseline to 4 weeks in the mobility of the arms. In all tests to be performed, a *p* value < 0.05 (with two tails) will be considered statistically significant, and confidence intervals will be reported.

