### 3.2. Primary Outcome

Before the start of the CR program and after the completion of the intervention program for both groups, we will evaluate health-related quality of life by means of the Short Form Health Survey-36 Questionnaire (SF-36). The SF-36 is an assessment tool used by a multitude of research teams in the evaluation of health-related quality of life in patients with heart disease. The SF-36 questionnaire aims at two different constructs to measure health-related quality of life: the physical component and the mental component. It comprises 35 scoring items, divided into eight dimensions: physical function, physical role, emotional role, social function, mental health, general health, body pain and vitality. The outcome measurements and instruments are synthetised in Table 3.

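### The stated primary analysis names no between-group contrast and is not on the primary outcome; applied to SF-36, its group-by-time form would be less precise than baseline-adjusted ANCOVA

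*Protocol article*

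**What the plan says.** Section 2.3.7 states: "The primary hypothesis will be examined by analysis of variance by repeated measurements to assess postoperative changes from baseline to 4 weeks", and the sentence ends "in the mobility of the arms". It adds a two-sided 0.05 level and confidence intervals. It mentions no group factor, group-by-time interaction or difference between arms, and the article writes no comparative hypothesis elsewhere.

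The design is comparative. Section 2.3.6 says "The participants will be randomly assigned into two groups", one using the CardioVR-ReTone system and one receiving usual rehabilitation, "via block randomisation on a 1:1 basis".

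Sections 3.1 and 3.2 make quality of life the primary outcome. SF-36 is to be measured "Before the start of the CR program and after the completion of the intervention program for both groups", so each patient in either arm has one baseline and one follow-up value. Table 3 has rows for quality of life, sternal stability, EMG muscle function, pain, exercise volume, cardiac response and adherence. It has none for arm mobility.

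**The concern.** The sentence fixes a method, a purpose and a variable. The purpose is change over time. Both arms receive rehabilitation after sternotomy, so change is to be expected in both whether or not the device adds anything. The variable is not the declared primary outcome.

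A repeated-measures ANOVA in a two-group trial yields three tests: time, group, and group by time. They answer different questions and have very different power. If the decisive one is not named, the conclusion can depend on a choice made after the data are seen.

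Even on the natural reading, group by time on SF-36, the plan gives up precision that a trial of about 15 per arm can hardly spare, although the baseline value it needs is already to be collected.

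**Working it through.** **Inputs from the article.** Expected sample size: five per month for 6 months, 5 × 6 = 30 (section 2.3.1), hence 15 per arm at 1:1. This reproduces the stated 30. It is a recruitment figure; the article gives no power calculation, effect size, SD or correlation to reproduce. Two-sided level 0.05 (section 2.3.7). One SF-36 before and one after (section 3.2).

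**Assumptions.** Correlation ρ between baseline and follow-up of 0.3, 0.5 or 0.7; equal SDs at both times, with the SD as unit; common recovery of 0.5 or 1.0 SD; true group difference of 0 or 0.8 SD; no dropout.

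**Step 1: the time effect when the device does nothing.** The SE of the mean change in 30 patients is √(2(1−ρ)/30). For a recovery of 0.5 SD the noncentrality is:

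- ρ = 0.3: 0.5/√(1.4/30) = 2.31
- ρ = 0.5: 0.5/√(1.0/30) = 2.74
- ρ = 0.7: 0.5/√(0.6/30) = 3.54

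In 20,000 simulated trials per setting, with 28 degrees of freedom, the time effect reached p < 0.05 in 61%, 75% and 93%. With a recovery of 1.0 SD it did so in at least 99%. In the same trials, group by time and ANCOVA both rejected in about 5%.

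**Step 2: precision of the two between-group tests.** With two time points, group by time is the t-test on change scores.

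- Change score: variance factor 2(1−ρ), 28 df.
- ANCOVA on baseline: variance factor (1−ρ²), 27 df, multiplied by 1 + 1/(N−4) = 1 + 1/26 for estimating the slope.
- Ratio ANCOVA/change: (1+ρ)/2 × (27/26).
- SE of the group difference: √(variance factor × 2/15), with the slope term included for ANCOVA.

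At ρ = 0.3, for example, the change-score SE is √(1.4 × 2/15) = 0.432 and the ANCOVA SE is √(0.91 × 2/15 × 27/26) = 0.355. Power comes from the noncentral t distribution.

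| ρ | Variance ratio without slope cost | With slope cost | SE change | SE ANCOVA | Power for 0.8 SD: change / ANCOVA | Difference detectable at 80% power: change / ANCOVA |
|---|---|---|---|---|---|---|
| 0.3 | 0.65 | 0.675 | 0.432 | 0.355 | 43% / 58% | 1.25 / 1.03 SD |
| 0.5 | 0.75 | 0.779 | 0.365 | 0.322 | 56% / 67% | 1.06 / 0.94 SD |
| 0.7 | 0.85 | 0.883 | 0.283 | 0.266 | 78% / 83% | 0.82 / 0.77 SD |

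Simulation agreed: 42%, 56% and 78% for group by time; 58%, 67% and 82% for ANCOVA. The group main effect, which averages over both time points, had only 26%, 24% and 21%.

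**Step 3: where the gain ends.** Setting (1+ρ)/2 × 27/26 = 1 gives ρ = 52/27 − 1 = 0.93. With an assumed 20% dropout (12 per arm, N = 24) the factor is 1 + 1/20 and the limit is 2/1.05 − 1 = 0.90.

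**The case against.** The strongest reply is that this is a condensed article. Model terms are commonly left to the full protocol or analysis plan, and a repeated-measures ANOVA in a two-group trial ordinarily includes group and group by time. That stands against one tempting reading. A reader might infer that the trial plans no randomised comparison at all, or that the investigators would take a time effect as evidence for the device. The sentence names no contrast, but it excludes none, and nothing in the article says how a time effect would be interpreted. The reply does not cover the rest: the article itself states the purpose and the variable, and the variable contradicts its own primary outcome.

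Second, ANCOVA is a matter of efficiency. Group by time is a valid randomised comparison that holds its 5% level. This is right, and the gain depends on a correlation that the article does not give: variance falls by about 32% at ρ = 0.3, 12% at 0.7 and only about 1% at 0.9.

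Two further inferences are not supported:

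- **A low correlation because surgery lies between the two SF-36 measurements.** Section 3.2 puts the baseline before the rehabilitation programme, which section 2.3.6 starts on day 2 after surgery. The preoperative evaluation listed under Figure 5 does not include SF-36. The baseline may fall on either side of surgery, so no part of the range of ρ is favoured.
- **That ANOVA loses patients whom ANCOVA would keep.** Simple ANCOVA drops the same patients without a 4-week value, so missing data do not separate the two.

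**Conclusion.** The point holds in two parts of unequal weight.

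The first rests on the text alone. The only stated primary analysis is on a variable that is neither the primary outcome nor in the outcome table, and it does not say which contrast decides the primary hypothesis. This needs correcting before analysis. The time-effect rates show what is at risk if the sentence is followed literally; they rest on the assumed recovery and correlations and do not predict what the investigators will do.

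The second is a recommendation. Once the analysis is directed to SF-36, baseline adjustment is more precise than group by time for any correlation below about 0.93 at N = 30. For an assumed 0.8 SD effect the gain in power is about 15, 11 and 5 percentage points at ρ = 0.3, 0.5 and 0.7, assuming equal SDs and full follow-up. It is a gain over a valid test, not the repair of an invalid one.

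**What to change.** Reconcile section 2.3.7 with sections 3.1 and 3.2 so that the primary analysis is on the declared primary outcome. If arm mobility is to be analysed as well, list it in Table 3 with its instrument and give it its own, non-primary analysis.

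State the primary analysis as the between-group difference in one named SF-36 score at the 4-week follow-up, estimated by ANCOVA with randomised group and the baseline value of the same score, and reported with a 95% CI. State that time effects and within-group changes are descriptive only.

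The cost is wording and one degree of freedom (27 instead of 28). SF-36 is already planned before and after the programme in both groups, so no extra patient, visit or measurement is needed.

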### 3.1. Outcome Measures

The primary outcome measurement is the modification of life quality at the end of the CR exercise training program. Secondary outcomes will encompass measurements of sternal stability, muscular activity (EMG signals) and pain level. Table 2 represents a framework for the schedule of outcome assessments.

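### No single SF-36 score is fixed as primary, every test is judged at two-sided 0.05, and the primary hypothesis is attached to arm mobility, which is not a listed outcome

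*Protocol article*

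**What the plan says.** Three parts of the protocol article bear on the primary claim.

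- **Outcome.** Section 3.1: "The primary outcome measurement is the modification of life quality at the end of the CR exercise training program". Section 3.2 and Table 3 give SF-36 as the instrument. Section 3.2 says that it addresses "two different constructs to measure health-related quality of life: the physical component and the mental component", and continues: "It comprises 35 scoring items, divided into eight dimensions". No component, dimension or total is singled out.
- **Test.** Section 2.3.7: "The primary hypothesis will be examined by analysis of variance by repeated measurements", applied to "changes from baseline to 4 weeks in the mobility of the arms". Arm mobility is absent from the outcomes in the Abstract, Sections 3.1 to 3.3 and Table 3. Section 2.3.5 has cameras recording movement, but no mobility outcome is derived from them.
- **Threshold.** Section 2.3.7: "In all tests to be performed, a *p* value < 0.05 (with two tails) will be considered statistically significant". The sentence also promises confidence intervals.

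The version of the instrument varies too. Section 2.3.6 has "Short Form Health Survey (SF-36v2) for evaluating the QoL", while Section 3.2 and Table 3 say SF-36 without a version.

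**The concern.** A primary outcome should be one variable with one test, or several with a stated rule for combining them. Here the declared outcome is a questionnaire that yields up to ten scores. The only primary test described is on a different variable. The only significance rule covers all tests alike. An analyst who followed the text could test each SF-36 score at 0.05 and present whichever reached significance as the primary result, and nothing written would rule that out.

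The trial expects 30 participants (Section 2.3.1), patients know their allocation (Section 2.3.6), the outcome is self-reported, and the stated aim is to validate a prototype. A chance difference on one dimension could be read as validation.

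**Working it through.** **Inputs.** The per-test level is 0.05, two-sided (Section 2.3.7). The number of scores is k = 2 components or k = 8 dimensions (Section 3.2). The correlation r between test statistics is not given in the documents, so it is assumed and varied from 0 to 0.9.

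**The plan's own figure.** The article states a per-test level but no overall error rate, so there is nothing to reproduce beyond the single-test case: 1 − (1 − 0.05)^1 = 0.05.

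**Independent scores.** If any significant score counts, the chance of at least one false positive under the null is 1 − 0.95^k.

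- k = 2: 1 − 0.9025 = 9.75%
- k = 8: 1 − 0.6634 = 33.7%

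**Correlated scores.** Each statistic is simulated as √r·F + √(1 − r)·E, where F is shared and E is specific to the score, both standard normal. A result is significant when its absolute value exceeds 1.96. There were 400,000 draws per setting.

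| Assumed correlation | Two components | Eight dimensions |
|---|---|---|
| 0 | 9.75% | 33.7% |
| 0.3 | 9.5% | 29.9% |
| 0.5 | 9.1% | 25.0% |
| 0.7 | 8.4% | 19.1% |
| 0.9 | 7.0% | 11.9% |

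Relative to 5%, two components give at most 9.75/5 = 1.95 times. Eight dimensions give between 11.9/5 = 2.4 and 33.7/5 = 6.7 times.

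**All ten scores.** Treating ten scores as independent gives 1 − 0.95^10 = 40.1%, but that ignores any overlap between components and dimensions. If each component is modelled as an equal-weight sum of four dimensions (an assumption), the ten-score rate is about 31%, 25% and 19% at correlations 0.3, 0.5 and 0.7. That is hardly more than the eight dimensions alone, so the range for eight dimensions is the one to use.

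**Only results favouring the device.** Eight dimensions give 18.4% if independent, 12.6% at correlation 0.5 and 6.0% at 0.9. The reference is then 2.5% for one test, so the ratio is 18.4/2.5 = 7.4 down to 6.0/2.5 = 2.4. The absolute figures roughly halve, but the inflation relative to one test remains.

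**After the fix.** One prespecified score gives 5%. Two components at 0.025 each give 1 − 0.975² = 4.94% if independent, and never more than 5%.

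**The case against.** The strongest reply is that the article never says one significant SF-36 score makes the trial positive. Section 2.3.7 sets a threshold for calling a test significant, and Section 3.2 describes a questionnaire; neither makes ten scores co-primary. Taken literally, the single primary test is the analysis of arm mobility, at 5%. Multiplicity handling is commonly left to an analysis plan that is not shown. The Conclusions also defer evaluation of cardiovascular benefit until feasibility has been demonstrated.

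Much of this stands. A reader might infer that the false-positive rate of the primary claim is several times 5%. The documents do not support that as a fact about the plan: it holds only if any score may carry the claim and if eight or more scores are tested. A reader might also quote 40% for ten scores, which treats the components as independent of the dimensions. Adding the secondary outcomes to the count would give a larger figure still, but secondary tests do not change the error rate of the primary claim. In addition, the note to Figure 5 places the EMG, heart rate, saturation and pain recordings within the device sessions, so a between-group test of each is not established.

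Two things survive. The identity of the primary variable belongs in the protocol and cannot be excused as analysis-plan detail. The arm-mobility sentence does not rescue the plan: it gives a test to an unlisted variable and leaves the declared outcome without one. The 0.05 rule is also stated for all tests, so an analysis plan that adjusted would depart from the published text.

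**Conclusion.** The point holds in conditional form. The protocol fixes no primary SF-36 score, judges every test at two-sided 0.05, and ties the primary hypothesis to a variable outside its outcome list. That contradiction and the unfixed score are matters of text and need no assumption.

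The size does rest on assumptions: that any one score could carry the claim, and that correlations lie between 0 and 0.9. On that basis the chance of at least one false-positive primary result is about 7–10% for the two components and 12–34% for the eight dimensions, against 5% for one prespecified score. The version label does not affect the error rate, but it should be settled at the same time because it is part of defining the variable.

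**What to change.** In Sections 2.3.7, 3.1 and 3.2:

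1. Name one SF-36 score, one version of the instrument and the 4-week time point as the only primary variable tested at two-sided 0.05. The Physical Component Summary is one reasonable choice, but the documents do not dictate it. Alternatively, test both components at 0.025 each.
2. Replace arm mobility in Section 2.3.7 with that variable, so that outcome and test agree.
3. Limit the significance rule to the primary variable. Report the remaining SF-36 scores and the secondary outcomes as estimates with 95% confidence intervals, labelled exploratory. Section 2.3.7 already promises intervals.
4. Use the same version label in Sections 2.3.6 and 3.2 and in Table 3.

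The cost is wording. The small downside is that a benefit seen only on a non-primary score would not count as the primary result. Splitting the level also costs power. With 30/2 = 15 per group and a two-group normal approximation, going from 0.05 to 0.025 lowers power on one component from 28% to 19%, 59% to 48%, or 78% to 69% at assumed standardised differences of 0.5, 0.8 and 1.0.
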